## Background

A living donor kidney transplant is the best treatment option for a patient with end-stage kidney disease (ESKD) as it provides better patient and graft survival and quality of life than either dialysis or a deceased donor transplant [1–13]. However, living donors (LDs) must undergo a major operative procedure associated with morbidity and mortality and the potential for adverse long-term consequences of living with a single kidney [14–58]. Practice guidelines, including those by the Kidney Disease: Improving Global Outcomes (KDIGO) consortium, allow a donor’s glomerular filtration rate (GFR) threshold to be as low as 60 ml/min/1.73m^2^ as an acceptance criterion for donation[59, 60]. The British Transplant Society 2018 guidelines and the European Renal Best Practice 2013 guidelines even allow GFR below 60 ml/min/1.73m^2^ in older donors[61, 62]. Since postdonation GFR is about 65% of the predonation value due to hypertrophy of the retained kidney, many LDs will have a GFR less than 60 ml/min/1.73m^2^ early after nephrectomy. For others, a decrease of GFR with aging or new onset disease will subsequently result in GFR less than 60 ml/min/1.73m^2^. Numerous studies in the general population have shown that individuals with GFR of less than 60 ml/min/1.73m^2^ have increased long-term risks including continuing loss of kidney function and higher rates of cardiovascular disease (CVD) and mortality [63–87]. Those observations may not be relevant to LDs who have an abrupt, isolated reduction in GFR in the absence of any underlying disease process or comorbid illness [88–93].

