### Aims and hypotheses

The MARKD study aims to determine long-term attributable LD risk by comparing well-matched controls with LDs. LDs will be compared with matched controls to determine: (a) whether LDs are at greater risk for the rare outcomes of mortality and ESKD; (b) whether LDs are at increased risk for CVD, cardiovascular mortality, and/or increased risk of intermediate measures of kidney disease (proteinuria, CKD [eGFR < 45 and eGFR < 30 ml/min/1.73m^2^ ]); (c) whether the trajectory of eGFR differs between LDs and controls; d) whether there are differences in the above outcomes for those developing de novo kidney disease and/or disease that might affect the kidneys (e.g., hypertension, DM, proteinuria); and e) whether there are differences in pregnancy outcomes (e.g., preeclampsia) between LDs and controls. The overall hypothesis is that LDs will have relatively small, slightly increased, but clinically insignificant, differences in the incidence of ESKD, mortality, intermediate endpoints, and pregnancy complications compared to well-matched control groups.

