#### Statistical analyses details

Log-rank tests and Kaplan Meier curves will be used as preliminary assessments to compare the risk of all-cause mortality and cardiovascular mortality, CVD, ESKD, CKD (eGFR < 45; eGFR < 30 ml/min/1.73m^2^), proteinuria, DM, and hypertension after index date between LDs and healthy controls. Our study is powered based on these analyses. Cox proportional hazards models will also be used to test for an increased risk of adverse outcomes in living LDs versus controls while directly accounting for the variables used for matching (to account for any possible residual imbalance between the cohorts similar to how one may adjust for characteristics in a randomized controlled trial to account for residual imbalance and to improve efficiency). In analyses involving Mayo LDs and their associated controls we will account for donation center (Mayo vs. UMN) as a covariate in the model. If the proportional hazards assumption fails, an alternative method such as an accelerated failure time model will be considered. Indeed, the risk of mortality and ESKD may disproportionately increase with long-term follow-up on the 60-year scale of this study [123, 130, 131]. A similar approach will be used to test for increased risk of outcomes for LDs versus controls after development of DM, hypertension, proteinuria, de novo kidney disease, or pregnancies with gestational hypertension or preeclampsia, but additional measures (e.g. matching, adjustment) will be used to account for the time of disease onset.

In order to evaluate biases in the selection of controls and ascertain outcomes, we will compare the risk of non-kidney-related cancer between donors and controls using the previously described methods. As cancer risk is lower in donors than the general population, we expect a similar lower risk in controls [150]. If controls are well matched, we do not expect the risk of non-kidney related cancer to differ between donors and controls. If a difference in cancer risk is identified, it may indicate imbalance in our matching and it will be further investigated using methods described in Shi et al. [151].

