A major innovative aspect of our study is our contemporaneous healthy matched control cohort. Unlike prior studies, we will more clearly delineate matched controls that reflect the health status of donors just prior to the date of donation. This will be accomplished by identifying controls known to be healthy and with normal renal function at the index date (matched to donation date) who are from the same geographical region of residence (Upper Midwest) as donors, and by obtaining granular data on controls to allow for optimal matching of controls to LDs on key characteristics (including family history of CKD).

Longitudinal follow-up of both LDs and REP controls provides detailed, uniquely available health information on events preceding ESKD and mortality. In contrast to previous studies, we will compare LDs and healthy-matched REP controls on the much more common intermediate endpoints (e.g., low GFR; CVD) that occur before ESKD or death. Additionally, we will be able to study outcomes of LDs who develop new comorbidities late after donation (e.g., obesity, hypertension, DM, early or late GFR < 45 ml/min/1.73m^2^, proteinuria). This will provide information about whether the impact of these comorbidities differs for those with 1 vs. 2 kidneys. That is, we will be able to assess if differences in long-term outcomes between donors and controls are mediated by differences in postdonation comorbidities.

We will be among the first studies to evaluate modifiers of the effect of donation on ESKD and mortality. There have been several studies of risk factors for developing ESKD in the donor population. However, these identified risk factors are also risk factors for ESKD in the general population. By using well-matched REP controls, we will be able to assess the effect of donation for “ideal” LDs and for LDs who, at donation, have risk factors for CKD. That is, ours will be among the first studies to test if the attributable risk of an outcome with kidney donation is modified by clinical and demographic factors (e.g., age, BMI, smoking, donation eGFR).

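### The comparison of donors and controls after a comorbidity has started tests effect modification, not the mediation that the Discussion attaches to it; GFR below 45, if used as a starting event, also means different things in the two groups

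*Protocol article*

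**What the plan says.** **The analysis.** After the main survival comparisons, Statistical analyses details in the protocol article states: "A similar approach will be used to test for increased risk of outcomes for LDs versus controls after development of DM, hypertension, proteinuria". The list goes on to de novo kidney disease and hypertensive pregnancies. The one stated safeguard is "but additional measures (e.g. matching, adjustment) will be used to account for the time of disease onset".

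**The aim.** Aim (d), in Aims and hypotheses, asks "whether there are differences in the above outcomes for those developing de novo kidney disease and/or disease that might affect the kidneys". Mediation is not mentioned there.

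**The interpretation.** The Discussion first writes "This will provide information about whether the impact of these comorbidities differs for those with 1 vs. 2 kidneys". The next sentence, introduced as a restatement, says "we will be able to assess if differences in long-term outcomes between donors and controls are mediated by differences in postdonation comorbidities".

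**GFR below 45.** The Discussion's list of new comorbidities includes "early or late GFR < 45 ml/min/1.73m^2^, proteinuria", and Aims and hypotheses counts eGFR below 45 as CKD. The Background says that "postdonation GFR is about 65% of the predonation value due to hypertrophy of the retained kidney". On the risks seen at low GFR in the general population, it says: "Those observations may not be relevant to LDs who have an abrupt, isolated reduction in GFR in the absence of any underlying disease process".

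**The concern.** Mediation asks how much of any donor excess arises because donation makes hypertension, diabetes or kidney disease more frequent. A comparison confined to people who already have the condition holds that frequency fixed, so the pathway of interest is absent from the contrast. What remains is whether donors fare worse than controls once both are affected. That is a useful question, but a different one.

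A ratio near 1 after onset could then be taken as evidence that comorbidities do not carry donor risk, when it fits equally well with their carrying all of it. The study is meant to inform donor candidates and long-term follow-up of donors, so the distinction matters.

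Selecting on a post-donation event also brings its own bias. If donation raises the incidence of a condition, affected donors need fewer other risk factors to have reached it than affected controls do. Accounting for time of onset does not address this.

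GFR below 45 adds a further difficulty. In donors the state is produced wholly or partly by removal of a kidney. In controls it is loss of function with two kidneys in place. Healthy donor tissue would be set against diseased control tissue, which would tend to understate harm.

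**Working it through.** **1. The plan's own figure for this analysis.** The Power section takes 240 matched pairs (480 people), CVD after diabetes in 15% to 23%, 5% type-1 error and 80% power. With Schoenfeld's formula (two-sided, 1:1), HR = exp[(1.960 + 0.842) / √(events × 0.25)]:

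- 480 × 0.15 = 72 events: exp(2.802/√18) = 1.94
- 480 × 0.23 = 110.4 events: exp(2.802/√27.6) = 1.70

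Both match the stated 1.94 and 1.70. The power statement is sound, and it concerns a donor-versus-control contrast after onset.

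**2. What that contrast estimates.** Assume an outcome hazard of 0.4% per year, multiplied by 4 after onset and by d as a direct effect of donation. After onset the ratio is (0.4% × 4 × d) / (0.4% × 4) = d. The factor by which donation raises comorbidity incidence does not appear.

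A simulation with assumed values (400,000 per arm, 40 years, comorbidity incidence 1% per year in controls) agrees, within simulation error:

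| Effect of donation | Mediated share | Overall rate ratio | Post-onset ratio |
|---|---|---|---|
| Doubles comorbidity, no direct effect | 100% | 1.25 | 1.00 |
| None | none | 1.00 | 1.00 |
| Direct effect 1.3 only | 0% | 1.28 | 1.29 |
| Direct effect 1.3, doubles comorbidity | 52% | 1.61 | 1.32 |

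The first two rows cannot be told apart after onset. The last two give nearly the same ratio with 0% and 52% mediated.

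**3. Selection on onset.** Add an unmeasured factor, present in half of each arm, that multiplies both the comorbidity and the outcome hazard. Donation has no direct effect.

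| Factor; effect on comorbidity | Share with factor among the affected (donors / controls) | Overall ratio | Post-onset ratio |
|---|---|---|---|
| ×3; doubled | 0.60 / 0.65 | 1.25 | 0.96 |
| ×5; tripled | 0.57 / 0.69 | 1.31 | 0.85 |

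A wholly mediated harm then looks like protection after onset. The strengths are assumptions; the direction is what matters.

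**4. GFR below 45.** Using the Background's 65%:

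- 45 / 0.65 = 69.2: a predonation GFR below this gives a value under 45 from surgery alone.
- 60 / 0.65 = 92.3: the equivalent for 60.
- 60 × 0.65 = 39: a donor at the lowest GFR named in the cited KDIGO criterion.

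The article does not give predonation GFR. Table 1 has mean creatinine, but not by sex and age. Assuming a normal predonation GFR, the share below 45 at once is Φ((69.2 − mean)/SD):

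- mean 105, SD 12: 0.1%
- mean 100, SD 15: 2.0%
- mean 90, SD 18: 12%

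The Power section says that 13.5% of UMN donors developed eGFR below 45 in follow-up. Against that, the immediate share runs from about 1% (0.14/13.5) to 92% (12.43/13.5). The article does not settle it.

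**The case against.** The strongest reply is that the planned analysis fits its aim. Aim (d) asks about outcomes among those who develop disease, the statistical section tests that, the Power section sizes it that way, and the Discussion first names the right question. Mediation appears once, in the Discussion, and an article may leave a mediation model to a fuller plan. All of this stands except the last step. The Discussion does not refer to a further model; it offers mediation as another way of saying what the post-onset comparison shows. That is a misstatement, not an omitted detail.

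A reader might infer that the plan compares the groups only after onset. It does not. Statistical analyses details also compares mortality, CVD, ESKD, CKD, proteinuria, diabetes and hypertension from the index date. The total effect and the link from donation to comorbidity are both estimated; they are simply never combined. Nor does the article say that a null post-onset result would be read as no mediation. That is a risk of the wording.

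On GFR, the post-onset list in the statistical section does not name GFR below 45; it says de novo kidney disease, which does not naturally describe a surgical fall. The Discussion's split into early and late suggests some awareness of the issue, though neither term is defined. The secondary point is therefore conditional on GFR below 45 being used as a starting event. A reader might also infer that many donors cross 45 at surgery. The Background says many only for 60. Any single figure for that share, or for the resulting bias in a hazard ratio, would rest on inputs that the article does not give.

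**Conclusion.** The main point holds as one of interpretation. The Discussion's mediation statement is not supported by the post-onset comparison, which conditions on the proposed mediator and returns a ratio near 1.0 under both full mediation and no donation effect. That follows from the structure of the contrast and does not depend on the simulated rates. The possible appearance of protection (0.96 to 0.85 in the examples) does depend on the assumed strength of an unmeasured factor.

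The secondary point holds conditionally. If GFR below 45 starts the clock, the event is wholly or partly surgical in donors and a two-kidney loss in controls, and accounting for time of onset leaves that difference in place. Its size is undetermined: about 0.1% to 12% of donors below 45 at once for an assumed mean predonation GFR of 90 to 105 and SD of 12 to 18. The expected direction is an understatement of harm. No stated power or sample-size figure is wrong on this account.

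**What to change.** **Mediation.** Either delete the mediation statement from the Discussion, label the post-onset analysis as prognosis after onset or effect modification, and note that it conditions on a post-donation event; or, if mediation is to be claimed, specify an analysis in the full matched cohort from the index date, with comorbidity onset as a time-varying mediator, reporting total, direct and indirect effects. The first costs a few words. The second needs moderate extra modelling. It would be confined largely to UMN donors and their controls, because Mayo donors are not surveyed. It must also cope with Table 2's uneven laboratory schedule: requested every 3 years in donors, recorded yearly in controls where available.

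**GFR-based onset.** Define it by decline from each person's own reference value: post-nephrectomy in donors, index in controls. Report donors below 45 from the outset separately. Alternatively, leave GFR below 45 out of the post-onset comparison. Merely requiring a first post-index value of at least 45 would not suffice, since a donor starting at 46 crosses after a trivial fall. The cost is fewer donor events and the loss of controls without a baseline creatinine, which the article says is common in younger controls.

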### Outcomes

Outcomes include mortality, CVD and cardiovascular mortality, serial creatinine (to determine eGFR trajectory and chronic kidney disease) and other laboratory measures, pregnancy outcomes and complications, and development of diseases that frequently lead to CKD (e.g., hypertension, DM, and obesity). Outcomes will be ascertained from national registries, medical record review of donors and REP controls, and a new survey administered to both donors and controls. A list of data collected, data source, and frequency of data collection is provided in Table 2 and is summarized below.

**Table 2 Tab2:** Data collection sources and frequency for REP controls and UMN donors. CR: Chart Review, DS: Donor survey + chart review if available (every 3 years), SS: Study Survey, LD: Lab data (every year)

	Source of data	
Data	UMN Donors	REP Controls

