**Outcomes**		
CVD^6^	DS, SS	CR, SS
Diabetes	DS, SS	CR, SS
Cancer	DS, SS	CR, SS
Hematuria	DS, SS	CR, SS
High cholesterol treated with medication	DS, SS	CR, SS
Hypertension treated with medication	DS, SS	CR, SS
Pregnancy history^7^	DS, SS	CR, SS
Proteinuria	DS, SS	SS
Kidney disease/ abnormal kidney function/ ESKD	DS, SS, USRDS	CR, SS, USRDS
Vital status and cause of death	DS, SS, NDI	CR^8^, SS, NDI

^1^ Chart review for controls includes abstraction of data from electronic transfer from the Rochester Epidemiology Project (REP) database, Mayo clinic paper records, Olmstead Medical Center electronic and paper record, Olmstead Community Hospital electronic and paper records, Epic, and the REP browser (electronic record system) from date of first REP encounter to date of last follow-up

^2^Permissible substance abuse at donation/donation is defined as a remote history of marijuana use with no active use around the time of the donation date or current marijuana use as long as it does not interfere with lifestyle. Remote other substance use is not a contraindication to donation as long as its truly remote

^3^Permissible depression/anxiety at donation/donation is defined as well controlled, in the distant past prior to the donation date, or involving few episodes of care

^4^Permissable hypertension at donation/donation includes that which is well controlled (< 140/90), treated with a diuretic antihypetensive agent, a non-diuretic antihypertensive agent, or both (1 diuretic and 1 non-diuretic hypertensive agent), age needs to be > 50 years. Exclude if age < 50 years or not well controlled or using 2 or more non-diuretic agents or using 2 or more diuretic agents

^5^Urine Dipstick, 24 H Urine Protein, Urinalysis Predicted 24-Hour Protein, Protein-Osmolality Ratio, Urine Protein to Creatinine Ratio, Urine Albumin to Creatine Ratio, 24 H Urine Albumin

^6^Congestive heart disease, myocardial infarction, cerebrovascular accident, transient ischemic attack, angioplasty, stents

^7^Number and year of pregnancies, pregnancy outcome (singleton, twins, triplets, ≥ 4, abortion, miscarriage, fetal death), gestational length (full term, pre-term), and pregnancy complications (gestational hypertension, gestational diabetes, proteinuria, eclampsia, preeclampsia)

^8^Proof of life noted for medical encounters with no data

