We will also evaluate if the effect of donation differs across baseline characteristics (i.e. evaluate if a characteristic modifies the effect of donation) by testing the significance of the interaction term between donation and the characteristic in the model. These models will also allow us to assess the attributable risk of donation in LDs with certain characteristics at donation. We will specifically assess if age, BMI, smoking, donation eGFR, and race/ethnicity modify the effect of donation on ESKD and mortality. As a sensitivity analysis, the analyses will be repeated using a subset of REP controls having at least 5 years of medical history preceding the index date.

Logistic regression models fit using generalized estimating equations will be used to test for differences in the odds of gestational hypertension and preeclampsia between LDs and controls for all pregnancies occurring after the index date, while accounting for women having potentially multiple pregnancies. Adjustment variables to be considered in the model include: race/ethnicity, age at pregnancy, gravidity, and previous occurrence of pregnancy complications. Secondary analyses using logistic regression models will test for differences in the odds of these complications in the first pregnancy after the index date, adjusting for having previous pregnancies, and second pregnancy after the index date, adjusting for the occurrence of pregnancy complications in the first post-index date pregnancy.

A linear mixed effects model will be used to test the difference in the trajectory of eGFR over time between living LDs and healthy controls. This model will initially have a linear effect for time with subject-specific random intercepts and slopes, but natural splines will be used to investigate nonlinear temporal trajectories.

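### The pregnancy-complication models count every post-index pregnancy, including abortions and miscarriages that cannot show the outcome; this dilutes any per-pregnancy risk and blurs the first- and second-pregnancy models

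*Protocol article*

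**What the plan says.** Under Statistical analyses details, a logistic model fitted by generalized estimating equations (GEE) compares the odds of each hypertensive complication in donors with the odds in "controls for all pregnancies occurring after the index date, while accounting for women having potentially multiple pregnancies". Secondary logistic models address the first and the second pregnancy after the index date. The second-pregnancy model adjusts for complications in the first post-index pregnancy. The candidate covariates for the GEE model are "race/ethnicity, age at pregnancy, gravidity, and previous occurrence of pregnancy complications". Neither pregnancy outcome nor gestational length is among them, and none of the three models carries a restriction on either.

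Table 2, footnote 7, defines the pregnancy history. It includes "pregnancy outcome (singleton, twins, triplets, ≥ 4, abortion, miscarriage, fetal death") and "gestational length (full term, pre-term").

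The Table 2 row for sources reads "Pregnancy history^7^ DS, SS CR, SS": the first pair is for University of Minnesota (UMN) donors, the second for Rochester Epidemiology Project controls. The legend gives "CR: Chart Review, DS: Donor survey + chart review if available (every 3 years), SS: Study Survey".

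**The concern.** Gestational hypertension and preeclampsia are, on their standard definition, conditions of later pregnancy; the article gives no definition of its own. A pregnancy ending in miscarriage or early abortion has no time in which either could be seen. Followed as written, the model still counts it, and always as a non-event.

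Three consequences need to be kept apart:

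- **Absolute risk.** Any risk per pregnancy taken from this set is diluted.
- **Pregnancy order.** A miscarriage can be the first post-index pregnancy. The first pregnancy truly at risk is then analysed as the second, with an adjustment covariate that says the previous one was free of complications.
- **Odds ratio.** If the two groups record early losses to different degrees, the comparison itself is distorted.

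Pregnancy outcomes are aim (e) under Aims and hypotheses, with preeclampsia as the example. The article also plans incidence rates for each outcome (Control groups for sensitivity analysis) and a risk calculator for candidate donors (Dissemination).

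**Working it through.** The article gives no event rate, early-loss share or power for the pregnancy outcomes, so there is no figure of its own to reproduce. The inputs below are assumptions: risk among pregnancies that can show the outcome p0 = 8% in controls; true odds ratio (OR) 1.0 or 2.0; early-loss share of recorded pregnancies m0 in controls and m1 in donors.

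**Formulas.** Observed risk in group g is q_g = p_g × (1 − m_g). Observed OR = [q1/(1 − q1)] / [q0/(1 − q0)].

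**Donor risk at a true OR of 2.0.** Control odds are 0.08/0.92 = 0.0870. Doubled, they are 0.1739, so p1 = 0.1739/1.1739 = 14.8%.

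**Dilution of absolute risk.** With m = 15%, 0.08 × 0.85 = 6.8%. With m = 25%, 0.08 × 0.75 = 6.0%.

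**Equal capture, m0 = m1 = 20%.** q0 = 0.0640 and q1 = 0.1185. The odds are 0.0684 and 0.1345, so the observed OR is 1.97. The risk difference falls from 14.8 − 8.0 = 6.8 points to 11.9 − 6.4 = 5.5 points.

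**Unequal capture:**

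| Donor m1 | Control m0 | True OR | q1 | q0 | Observed OR |
|---|---|---|---|---|---|
| 25% | 10% | 2.0 | 0.1111 | 0.0720 | 0.1250/0.0776 = 1.61 |
| 25% | 10% | 1.0 | 0.0600 | 0.0720 | 0.0638/0.0776 = 0.82 |
| 10% | 20% | 2.0 | 0.1333 | 0.0640 | 0.1538/0.0684 = 2.25 |
| 10% | 20% | 1.0 | 0.0720 | 0.0640 | 0.0776/0.0684 = 1.13 |

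**Another base risk.** At p0 = 5% the pattern is the same. Equal shares of 20% turn 5.0% into 4.0% and an OR of 2.00 into 1.98. Shares of 25% and 15% move a null OR to 0.88 when donors have the larger share and to 1.14 when controls do. Shares of 25% and 5% move it to 0.78 and 1.28.

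**Can capture differ?** The sources are not the same. Donors have repeated surveys, with chart review where available, plus the study survey; controls have chart review plus the study survey. The article does not say which combination records more early losses.

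**Pregnancy order.** Take a woman whose post-index pregnancies are a miscarriage and then a birth with preeclampsia. The first-pregnancy model scores her as a non-event. The second-pregnancy model scores an event after a pregnancy without complications. In fact the birth was her first pregnancy at risk. This arises even with equal capture.

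**The case against.** The best defence is that the wording about all pregnancies is there to contrast with the first- and second-pregnancy models: every pregnancy per woman enters, hence GEE. Footnote 7 lists what is collected, not what is analysed, and a full analysis plan could restrict the set. It could. But the article does state an analysis set, its own definition of a recorded pregnancy includes early losses, and nothing it lists removes them. That goes beyond a detail left open.

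A reader might infer that the odds ratio is biased, perhaps so as to hide harm to donors. The documents do not support that. With equal capture the change is negligible; the larger shifts rest on gaps of 10 to 20 percentage points that no document supplies, and they can go either way. The contrast in sources is also softer than the abbreviations suggest. The donor-survey code includes chart review where available, and Medical record review describes abstraction of donor records at survey time. Survey data says the same survey goes to both groups and presents it as giving uniform ascertainment. That narrows the gap without closing it: the survey reaches only people not known to have died, needs a reply, and adds to sources that still differ.

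Two further points stand. Risk per recorded pregnancy is a coherent quantity, though not the risk in a continuing pregnancy. And the pregnancy model reports odds; absolute risk enters only through the general commitments to incidence rates and a calculator, neither of which names this model. Finally, restricting to continuing pregnancies conditions on something that happens after donation, and could introduce selection if donation affects early loss.

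**Conclusion.** The point holds as a worthwhile, inexpensive improvement. As written, early losses enter as structural non-events in all three models. What follows with certainty is limited: any absolute risk per pregnancy is reduced by exactly the early-loss share (8% reads 6.8-6.0% at an assumed 15-25%), and the first- and second-pregnancy models can misplace the first pregnancy at risk. The effect on the odds ratio is conditional: about 2.00 to 1.97 with equal capture, and material only with unequal capture, whose presence, size and direction the documents do not establish.

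This rests on the standard late-pregnancy definition of both conditions and on assumed base risks and loss shares. It does not show that the planned odds ratio is wrong, or that it would favour either group.

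**What to change.** In Statistical analyses details:

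- Define the set for the main GEE model and both secondary models as post-index pregnancies not recorded as abortion or miscarriage. Keep births and fetal deaths.
- Number first and second pregnancy within that set. Earlier losses can still count towards gravidity.
- Report early losses by group and by data source as a separate outcome.
- Keep the all-pregnancies GEE model as a sensitivity analysis.

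The restriction should use the recorded pregnancy outcome rather than a gestational-age cut-off, because footnote 7 lists gestational length only as full term or pre-term. A late termination coded as abortion would be misclassified; the sensitivity analysis covers that.

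The cost is a few sentences and no new data. The downside is that the main analysis conditions on the pregnancy continuing. The separate report of losses shows whether that matters, and the all-pregnancies model shows how far the result depends on it.
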